**Ethics and dissemination:**

Approval for data collection, storage and release for research purpose has been given (6 May 2014, PAC38A/13) by the Privacy Advisory Committee. The results of this study will be disseminated through peer-reviewed publications in journals, national and international conferences.

Strengths and limitations of this studyThis is the first study evaluating the effectiveness and the cost-effectiveness of the Health in Pregnancy (HiP) grant in Scotland. It will use routinely available vital event and maternal and neonatal health records that are known to have high completeness and accuracy.The evaluation of the HiP grant using an interrupted time-series design will enable us to analyse birth weight trends in Scotland and detect whether the intervention has had an effect over and above the underlying temporal trend. The use of interrupted time series will overcome other biases such as the autocorrelation of repeated measurements (measurement taken close together are related), seasonal effects (birth weight varies according to month of birth), the duration of the intervention (we will have preintervention, intervention and postintervention), and random variation in the measurement (birth weight).This study will evaluate the effectiveness and the cost-effectiveness of the HiP grant, birth weight and other birth outcomes in Scotland using obstetric as well as maternal data. However, these outcomes may be influenced by many factors, not all of which are routinely captured (such as maternal diet, maternal work and psychological stress, abuse, exposure to toxic substance).^11^The HiP grant was money given to pregnant women with no constraint on its use. The use of routine data gives us no indication on how the money was spent.

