## Methods and analysis

### Study design

The HiP grant will be evaluated as a natural experiment using interrupted time-series analysis to compare outcomes before the introduction of the intervention in Scotland and immediately after its withdrawal with those during the period for which it existed.

The Medical Research Council (MRC) has issued guidelines regarding the use of natural experiments to evaluate population health interventions when exposure to the intervention has not been manipulated by the researchers (table 1).^35^
^36^

**Table 1 BMJOPEN2014006547TB1:** Guidance for use of natural experiments to evaluate population health interventions

When to use a natural experimental approach?	How does the evaluation of HiP grant meet these criteria?
There is a reasonable expectation that the intervention will have a significant health impact, but scientific uncertainty about the size or nature of the effects	The HiP grant represented an attempt to influence behaviour—appropriate and timely receipt of antenatal care advice. With the sample size we are using in this evaluation study, we are able to detect small changes in birth weight
Natural experimental study is the most appropriate method for studying a given type of intervention	The HiP grant was a universally applied cash transfer available for all pregnant women with no discrimination between socioeconomic classes. This policy was not introduced using a randomised allocation
It is possible to obtain the relevant data from an appropriate study population, comprising groups with different levels of exposure to the intervention	The uptake of the HiP grant was thought to be 98–99%. The linked Scottish birth data set has 98% coverage of births and the primary outcome, birth weight, is well measured, 99.9% complete and accurate. Exposure is determined by the dates for which the HiP grant was in existence
The intervention or the principles behind it have the potential for replication, scalability or generalisability	The HiP grant is replicable everywhere in countries with similar health systems

HiP grant, Health in Pregnancy grant.

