### Study population

The population under study will be all singleton births in Scotland over the periods of January 2004 to March 2009 (preintervention), April 2009 to April 2011 (intervention) and May 2011 to December 2013 (postintervention).

The Scottish maternity and neonatal database is a comprehensive record linkage system.^40^
^41^ Probabilistic linkage procedures are used to add a unique identifier to all data sets to ensure all relevant records relating to an individual can be linked as required. It facilitates the linkage of a number of records from the system of Scottish Morbidity Records (SMR) including mother's obstetric records (SMR02) and the baby's birth and neonatal information from Scottish Birth Records (SBR).^42^ Further links to the stillbirth and infant Death Survey and the National Records of Scotland (NRS) birth, stillbirth and infant death records can be carried out. The coverage is almost all births in Scotland.^43^ From NRS data, we know of all registered births in Scotland (ie, 100%). We have suitable record linked data on 98% of these births.^44^ These will nearly all be hospital births; a fairly high proportion of the missing records are home births.

There is an average of about 56 000 births per year in Scotland.^45^ The analysis period 2004–2013 should yield over 585 000 births. The analysis period 2006–2013 should yield over 455 000 births.

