### Sample size

The data are clustered in small areas, 6505 data zones. The sample size calculation takes this clustering into account. Assuming an average of 56 000 singleton live births per year, and allowing for the clustering within the 6505 data zones in Scotland (average population 780/data zone) with an estimated intraclass correlation coefficient of 0.05, we have power of 0.90 to detect an effect of 7 g change in birth weight at a 95% significance level. This is not to say that 7 g is a clinically important threshold; rather, it is indicative of the power of the study. The large national data set available to us will allow for subgroup analysis. In the 20% most deprived areas, we will have power of 0.80 to detect an effect of 13 g; among the 26% of single mothers, we will have power of 0.80 to detect an effect of 11 g. To put these small effects into context, 50 g is the estimated mean birth weight reduction reported in the meta-analysis of the effect of interventions in pregnancy on maternal and obstetric outcomes.^27^

We anticipate item non-response for some outcomes and explanatory variables. Our primary outcome measure, birth weight, has a completion rate of 99.9%. There is high completion rate (<1.5% missing) for all obstetric variables,^46^ with the exception of crown to heel length (15% missing) and head circumference (12% missing). The item non-response ranges from 8% for maternal smoking to 20% for marital status. We will use multiple imputation to account for missing data and all analyses will compare the results of analyses of complete cases and multiple imputation.^63^ Imputed models will be constructed such that they contain as many relevant predictor variables as possible. The more variables that are used the greater the amount of information available on which estimations are made. We will use all (or as many as possible) obstetric and maternal variables in an imputation model to predict the missing values. It is difficult to identify in advance the number of multiple imputed data sets we will need to construct but it is likely to be between 5 and 10. We will then analyse these data sets identically and combine the results to get the estimates and SEs for the multiple imputed data. These results will be compared with the complete case analysis results.

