### Data analysis plan

#### Statistical analysis

Descriptive statistics of all variables will be presented as mean, SD, minimum, median and maximum for continuous variables and as proportions when the variables are categorical.

The main statistical design we will use is interrupted time series.^64^ Segmented regression analysis will allow an estimation of the size of the effect of the HiP grant at different time points, as well as changes in the trend of the effect over time after its implementation.

Outcomes will be measured on individual births, which are nested within mothers, with mothers themselves clustered within data zones and Health Boards. Multilevel univariable and multivariable models will be used to determine whether the outcomes changed during the period in which the HiP grants were in effect. Multilevel linear regression will be used when the outcome is continuous and multilevel binomial logistic regression when the outcome is dichotomous. Multilevel multinomial logistic regression will be used for the multicategory outcomes mode of delivery and 5 min Apgar score.

All analyses will be adjusted for temporal trends and seasonal variations in outcomes in addition to maternal age, sex of child, parity, marital status, height, weight at booking, diabetes, smoking status, gestation at booking, maternal diabetes, social class, maternal smoking and area deprivation.

The effect of HiP grant on birth weight might have a carryover effect after the withdrawal of the grant. In other words, postintervention the slope in birth weight might not fall back to the same rate as preintervention. This could be due to women who have gave birth during the intervention subsequently having a birth postintervention but still heeding the health advice given during their first pregnancy. We will carry out an additional analysis only on primiparous women to avoid such contamination.

We will analyse preterm births stratified by mode of delivery and stratified according to whether the birth was induced or spontaneous.

We will repeat the main analyses including (ie, adjusting for the effect of) ethnicity along with other covariates and compare the results with analyses excluding ethnicity to gauge the impact of this on our results. We note that the quality of this variable (including the completeness of recording) is poorer than for other variables and that only 1–2% of mothers delivering in Scotland are from minority ethnic backgrounds.

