The simplest model for the intervention effect will include a dummy variable ‘intervention’ covering the period from the introduction to the withdrawal of HiP grants, with adjustment for relevant factors such as marital status. (More complex models of the effect of the intervention will include an interaction of the intervention with the temporal trend.) Before carrying out specific subgroup analysis, we will identify differential effects by fitting interaction terms. An assessment as to whether there is a differential effect of the intervention for single women, for example, will involve a test of the significance of the intervention between marital status and the intervention effect. If the interaction is significant this will aid our understanding of the generalisability to other populations, including the rest of the UK. Subgroup analyses will be conducted for those groups seen as having the greatest potential to benefit from the payments such as those living in the most deprived areas, those in the lowest social classes, lone mothers, primiparous women, teen mothers, mothers from ethnic minorities and selected combinations of these groups. For each group we will replicate the main analysis. This reduction in sample size for subgroup analyses will result in fewer women/births being available but the same number of areas (data zones) will be analysed (apart from analyses restricted to those living in the most deprived areas).

An increase in birth weight, although desirable at a population level, may not be a beneficial outcome if the baby were already at risk of being LGA. Separate subgroup analyses will therefore be conducted for women seen to be at high risk of delivering a LGA baby (women with diabetes) and for the remainder of the population. Given that some subgroups may contain small numbers, and bearing in mind the potential importance of the intervention, we will report the results of all subgroup analyses and not just those that reach statistical significance to avoid false negatives. The above process will involve conducting many tests, which will not be independent of each other. Rather than adjusting CIs or p values to account for this we will present the results of all analyses and caution the user regarding the interpretation of the results. Indeed, some statisticians recommend never correcting for multiple comparisons while analysing data.^65^

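### The grant varies only by calendar date, but no stated model term or test covers residual month-to-month variation, so the claim that the design overcomes autocorrelation is unsupported

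*Protocol article*

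**What the plan says.** - **Exposure.** Table 1 (Study design) says: "Exposure is determined by the dates for which the HiP grant was in existence". The Statistical analysis section enters it, in the simplest model, as one dummy variable "covering the period from the introduction to the withdrawal of HiP grants". More complex models add an interaction with the temporal trend.
- **Error structure.** The same section states: "Outcomes will be measured on individual births, which are nested within mothers, with mothers themselves clustered within data zones and Health Boards". Table 2, presented as the analysis plan, names multilevel linear, binomial logistic and multinomial logistic regression, with date of birth among the covariates.
- **Time.** "All analyses will be adjusted for temporal trends and seasonal variations in outcomes", together with maternal and area covariates. Segmented regression is named as the approach.
- **Claim.** The strengths and limitations box after the abstract says: "The use of interrupted time series will overcome other biases such as the autocorrelation of repeated measurements". It explains the term as measurements taken close together being related.
- **Power.** The Sample size section allows for clustering in 6505 data zones (intraclass correlation 0.05) and gives power 0.90 for a 7 g change.

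**The concern.** At any date, every data zone and Health Board in Scotland has the same grant status, and places in general contribute births to all three periods. Place effects therefore do not represent the uncertainty in a before, during and after comparison. The mother level covers siblings, not births to different women in the same month. Given mother, place and covariates, the stated model treats births as independent, so any national month-to-month departure from trend and season is taken as zero.

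The article itself lists changes that a smooth trend plus season need not capture: the March 2006 smoking ban, Healthy Start replacing the means-tested parts of the Welfare Food Scheme in 2006, and booking-policy changes discussed from 2008 and required by March 2011. If such departures leave runs of residuals with the same sign, the confidence interval for the overall grant effect is too narrow. The two-sided test for benefit or harm then rejects too often. The economic analysis and any recommendation to reintroduce a grant draw on that estimate.

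**Working it through.** **Inputs from the article**
- Months: 63 before, 25 with the grant, 32 after; 120 in all (Study population).
- Births: 56 000 a year, or 56 000/12 = 4667 a month (Sample size).

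**Assumed inputs, because the article gives none**
- Birth-weight SD: 500 to 560 g.
- SD of the shared monthly shock left after adjustment, tau: 0, 2 or 5 g.
- AR(1) correlation of that shock, rho: 0 to 0.6.

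**1. The plan's own power figure.** The SD is not stated, so there is no unique check. One set of inputs that comes close:
- Yearly cluster size 56 000/6505 = 8.6; design effect 1 + 7.6 × 0.05 = 1.38.
- Births: 25 × 4667 = 116 667 with the grant and 95 × 4667 = 443 333 without.
- With an SD of 550 g, SE = 550 × √[1.38 × (1/116 667 + 1/443 333)] = 2.13 g.
- 7/2.13 − 1.96 = 1.33, so power is about 0.91.

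No between-month variance enters this calculation.

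**2. Sampling variance of a monthly mean**
- SD 560 g: 560²/4667 = 67.2 g², so the SD of a monthly mean is 8.2 g.
- SD 500 g: 500²/4667 = 53.6 g², so it is 7.3 g.

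**3. Model.** The 120 monthly means are regressed on the intervention dummy, a linear trend and season, as a stand-in for the multilevel model.
- Naive variance: s²(X′X)⁻¹, with s² from step 2.
- True variance: (X′X)⁻¹X′VX(X′X)⁻¹, with V = s²I + tau² × AR(1)(rho).
- Naive SE of the grant effect: 1.70 g at SD 500 g and 1.90 g at SD 560 g.
- True type I error of a nominal 5% test: 2[1 − Φ(1.96/ratio)].

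**4. Results for the overall effect**

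| tau | rho | SE ratio, SD 560 g | Type I error | SE ratio, SD 500 g | Type I error |
|---|---|---|---|---|---|
| 0 g | any | 1.00 | 5.0% | 1.00 | 5.0% |
| 2 g | 0 | 1.03 | 5.7% | 1.04 | 5.9% |
| 2 g | 0.6 | 1.10 | 7.5% | 1.13 | 8.2% |
| 5 g | 0 | 1.17 | 9.4% | 1.21 | 10.6% |
| 5 g | 0.3 | 1.29 | 13% | 1.36 | 15% |
| 5 g | 0.6 | 1.53 | 20% | 1.64 | 23% |

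Hand check at rho 0: the ratio is √(1 + tau²/s²), for example √(1 + 25/67.2) = 1.17. A segmented level-and-slope model at SD 500 g gives similar ratios: 1.04 to 1.11 at 2 g and 1.21 to 1.57 at 5 g.

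**5. Subgroup of 20% of births.** The monthly sampling variance is five times larger (5 × 67.2 = 336 g² at SD 560 g). At tau 5 g the ratios 1.29 and 1.53 fall to about 1.06 and 1.13.

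**6. Interaction tests.** An additive shock that shifts all groups equally in a month cancels from the contrast between groups.

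**The case against.** **The risk is conditional.** The documents give no month variance and no autocorrelation, and the larger ratios need a 5 g shock with strong correlation, which no section supports. Trend, season and many covariates are adjusted for and may remove much of any shared shift. The mother level also deals with one reading of repeated measurements, namely births to the same woman. All of this stands. A reader might infer that the standard errors are too small as a matter of fact; the documents support only that they will be if shared variation remains.

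**The article condenses a fuller plan.** Residual checks are often left to the SAP, and listing nesting levels does not exclude them. This stands in part. However, the article fixes the levels, presents Table 2 as the analysis plan and states without qualification that autocorrelation is overcome. That claim has no support in the methods shown.

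**Two wider readings fail.**
- One might infer that the 7 g detectable effect grows by the ratios above. It does not follow, because 7 g comes from a data-zone calculation. The 120-month model has its own 90%-power detectable effect: at SD 560 g it is 6.2 g with no shock, about 7.9 g at tau 5 g with rho 0.3, and about 9.4 g with rho 0.6.
- One might infer that every outcome and subgroup suffers alike. Steps 5 and 6 show otherwise, and nothing was computed for the binary or multinomial outcomes.

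**Conclusion.** The point holds as a conditional weakness together with an unsupported claim, and it should be fixed. Exposure varies only by date, while the stated random levels are mother, data zone and Health Board. No stated term or test addresses residual monthly variation or serial correlation. If such variation remains, the standard error of the overall grant effect on birth weight is understated by a factor of 1.03 to 1.13 for a 2 g shock and 1.17 to 1.64 for 5 g. The true type I error is then about 6 to 8% and 9 to 23%. These figures rest on an assumed SD of 500 to 560 g and AR(1) correlation of 0 to 0.6; with no shared variation the error is nil. It matters because a shock of a few grams is not small beside the 7 g effect that the article uses to show its power.

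**What to change.** - Add calendar month as a crossed random effect, with AR(1) correlation if the residuals show it. Alternatively, fit the segmented model to the 120 covariate-adjusted monthly means with AR(1) or Newey-West errors.
- Report the residual autocorrelation.
- If month variation or autocorrelation is present, take the confidence interval and p-value for the overall grant effect from the time-robust error.
- Reword the strengths and limitations statement to say that autocorrelation will be modelled and checked, not that the design overcomes it.

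The cost is one extra random term or a 120-point regression, with no new data. Intervals may become wider.

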In the UK, the Health in Pregnancy (HiP) grant was introduced for women reaching the 25th week of pregnancy with a due date on/or after 6 April 2009. It was subsequently withdrawn for women reaching the 25th week of pregnancy on/or after 1 January 2011. The HiP grant was a universal conditional cash transfer of £190 for women reaching 25 weeks of pregnancy if they had sought health advice from a doctor or midwife. It was designed to provide additional financial support, in the last months of pregnancy, towards a healthy lifestyle including diet, and it was suggested that the link to the requirement for pregnant women to seek health advice from a professional may provide a greater incentive for expectant mothers to seek the recommended health advice at the appropriate time. The grant was paid and administered by Her Majesty's Revenue and Customs (HMRC) on receipt of a claim form partly completed by the midwife or doctor. Advice was offered as normal by doctors and midwives. Payment was made directly into a bank account with a telephone helpline available to provide support through the claims process including options for payment in the event of difficulties opening a bank account. Take-up of the HiP grant was similar to that of child benefit (98–99%, personal communication, HMRC).

The current study focuses on the evaluation of the effectiveness and cost-effectiveness of the HiP grant. As a primary outcome, we will consider the difference in birth weight for babies born to those mothers who were eligible for the HiP grant with babies born before the HiP grant was introduced or after it was withdrawn. Specific questions the research project will address are:
Were there differential impacts of the intervention for particular subgroups defined by socioeconomic (defined in terms of both area deprivation and individual occupational social class), demographic (marital status, age, maternal height), or obstetric (parity, previous caesarean section) factors or for selected combination of these groups?Was the HiP grant cost-effective? How did cost-effectiveness vary across important subgroups identified as having differential outcomes?

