### Outcome measures

#### Primary outcome

The primary outcome will be birth weight among singleton births. This is influenced by many factors including maternal nutrition and one of the intentions of the HiP grant was to improve this.

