#### Secondary outcomes

The following secondary outcomes will be assessed:
Gestation at booking;Booking before 25 weeks;Measures of size: crown to heel length, head circumference;Measures of stage: gestational age at delivery, weight-for-dates (standardised; SGA babies are those weighted less than the 5th centile weight, or LGA weighted more than the 90th centile weight), term at birth (preterm, babies are born at less than 37 weeks gestation; term babies are those born between 37 and 42 weeks gestation and post-term babies are born after 42 weeks gestation);Birth outcomes: mode of delivery, stillbirths, neonatal deaths, 5 min Apgar score. Although there is some debate concerning the robustness of the Apgar score as an outcome, it is in common use and we will therefore present results for this outcome within the context of the wide debate on the subject.

Due in part to the introduction of smoking ban in Scotland in 2006, an additional outcome of interest is maternal smoking. Maternal smoking is collected at booking and during pregnancy. The health advice given when receiving the HiP grant might have an impact on smoking rates during pregnancy over and above that of the smoke-free legislation. We will analyse the temporal change in smoking rate by socioeconomic class and its effect on outcomes.

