We will conduct sensitivity analyses to increase the probability that any observed effect can be attributed to the HiP grant. The timing of the HiP grant is well-defined and fixed, therefore using the interrupted time-series approach any effects within that window can be observed. We plan to carry out three analyses for this.
We will extend this window for some months before April 2009 (births before the HiP grant was introduced).We will extend this window for some months after April 2011 (births after the HiP grant was withdrawn).We will extend the window both before and after the HiP grant period. In each case we would expect to see a dilution of any effects of the HiP grant.

The statistical analysis plan detailing the outcomes and the covariates, which will be considered for adjustment in the statistical models are presented in table 2.

**Table 2 BMJOPEN2014006547TB2:** Analysis plan detailing the outcomes and the covariates that will be considered for adjustment in the statistical models

	Primary outcome	Secondary outcomes										
	Birth weight	Booking status		Measures of stage			Measures of size:	Other birth outcomes				Maternal smoking during this pregnancy
		Gestation at booking	Booking before 25 weeks	Gestational age at delivery	Term at birth	Weight-for-dates	Head circumference,	Mode of delivery	Stillbirth	5 min Apgar score	Neonatal death	
Covariates							Crown to heel length					
*I. Measured covariates*												
A. Sociodemographic determinants												
A-1. Related to the baby												
Date of birth	Χ	Χ	Χ	Χ	Χ	Χ	Χ	Χ	Χ	Χ	Χ	Χ
Sex	Χ			Χ	Χ	Χ	Χ	Χ	Χ	Χ	Χ	
Gestational age at delivery	Χ						Χ	Χ	Χ	Χ	Χ	
Birth weight							Χ			Χ	Χ	
Mode of delivery										Χ	Χ	
A-2. Related to the mother												
Hip grant	Χ	Χ	Χ	Χ	Χ	Χ	Χ	Χ	Χ	Χ	Χ	Χ
Age	Χ	Χ	Χ	Χ	Χ	Χ	Χ	Χ	Χ	Χ	Χ	Χ
Weight at booking	Χ	Χ	Χ	Χ	Χ	Χ	Χ	Χ	Χ	Χ	Χ	
Height	Χ			Χ	Χ	Χ	Χ	Χ	Χ	Χ	Χ	
Ethnic group	Χ	Χ	Χ	Χ	Χ	Χ	Χ	Χ	Χ	Χ	Χ	Χ
Parity	Χ	Χ	Χ	Χ	Χ	Χ	Χ	Χ	Χ	Χ	Χ	Χ
Marital status	Χ	Χ	Χ	Χ	Χ	Χ	Χ	Χ	Χ	Χ	Χ	Χ
Social class	Χ	Χ	Χ	Χ	Χ	Χ	Χ	Χ	Χ	Χ	Χ	Χ
B. Medical risks of the current pregnancy and before pregnancy												
Diabetes	Χ	Χ	Χ	Χ	Χ	Χ	Χ	Χ	Χ	Χ	Χ	
Hypertension	Χ	Χ	Χ	Χ	Χ	Χ	Χ	Χ	Χ	Χ	Χ	
Infection	Χ			Χ	Χ	Χ	Χ	Χ	Χ	Χ	Χ	
Congenital anomalies	Χ			Χ	Χ	Χ	Χ	Χ	Χ	Χ	Χ	
Induction of labour									Χ	Χ	Χ	
Duration of labour									Χ	Χ	Χ	
C. Medical risks related to previous pregnancies												
Previous spontaneous abortions		Χ	Χ						Χ			
Previous stillbirths		Χ	Χ						Χ			
Previous neonatal deaths		Χ	Χ								Χ	

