D. Environmental and behavioural risks												
Income domain of the SIMD	Χ	Χ	Χ	Χ	Χ	Χ	Χ	Χ	Χ	Χ	Χ	Χ
Urban/rural status of the area of residence	Χ	Χ	Χ	Χ	Χ	Χ	Χ	Χ	Χ	Χ	Χ	Χ
Booking status (gestational age at booking, booking before 25 weeks)	Χ			Χ	Χ	Χ	Χ	Χ	Χ	Χ	Χ	Χ
Smoking status (before and during this pregnancy)	Χ	Χ	Χ	Χ	Χ	Χ	Χ	Χ	Χ	Χ	Χ	
Typical weekly alcohol consumption (before and during this pregnancy)	Χ	Χ	Χ	Χ	Χ	Χ	Χ	Χ	Χ	Χ	Χ	Χ
Drug misuse during this pregnancy	Χ	Χ	Χ	Χ	Χ	Χ	Χ	Χ	Χ	Χ	Χ	Χ
*II. Unmeasured covariates*												
Maternal weight gain												
Maternal nutrition												
Maternal education												
Maternal exposure to stress												
Maternal physical activity												
Exposure to toxic substances												
Birth interval												
History of preterm birth												
Statistical methods												
Multilevel linear regression	Χ	Χ		Χ			Χ					
Multilevel binomial logistic regression			Χ			Χ			Χ		Χ	Χ
Multilevel multinomial logistic regression					Χ			Χ		Χ		

Χ: variables which will be considered for adjustment in the statistical analysis.

SIMD, Scottish Index of Multiple Deprivation.

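### The birth-weight models adjust for booking and smoking, and may adjust for gestational age, which the protocol also treats as outcomes of the grant; the coefficient may omit part of the total effect, of unknown size.

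*Protocol article*

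**What the plan says.** The Primary outcome section states: "The primary outcome will be birth weight among singleton births". The Introduction frames the question as the difference in birth weight between babies of eligible mothers and babies born before the grant began or after it ended.

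The Statistical analysis section then sets the adjustment without exception: "All analyses will be adjusted for temporal trends and seasonal variations in outcomes". Its covariate list continues with "height, weight at booking, diabetes, smoking status, gestation at booking, maternal diabetes, social class, maternal smoking and area deprivation". Smoking appears in it twice.

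Table 2 gives a longer, outcome-specific list. For birth weight it marks "Gestational age at delivery", the row beginning "Booking status (gestational age at booking, booking before 25 weeks", and smoking before and during the pregnancy. Its footnote is softer than the text: these are "variables which will be considered for adjustment in the statistical analysis".

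The same variables appear elsewhere as things the grant might change. The Introduction says the link to professional advice "may provide a greater incentive for expectant mothers to seek the recommended health advice at the appropriate time". The Secondary outcomes section lists gestation at booking, booking before 25 weeks and gestational age at delivery, and adds maternal smoking because "The health advice given when receiving the HiP grant might have an impact on smoking rates during pregnancy".

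**The concern.** A covariate that the intervention can change is a possible mediator. Conditioning on it takes out whatever part of the effect passes through it, so the coefficient no longer answers the question in the Introduction, which concerns the whole difference in birth weight. The plan does not say whether it wants the total effect or the effect net of booking, smoking and gestation.

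The protocol shows this caution at area level: it rejects the health domain of the deprivation index because that domain contains a low-birth-weight indicator. It does not apply the same reasoning to individual-level covariates that are themselves study outcomes.

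At stake is the primary estimate. The Economic analysis section takes the grant's effectiveness only from this study, so an effect that omits real pathways could also understate benefit in the cost-effectiveness model.

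**Working it through.** **1. The passages side by side**

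| Variable | As outcome or target of the grant | As adjuster for birth weight |
|---|---|---|
| Gestation at booking | Secondary outcome; timely advice is the targeted behaviour (Introduction) | Fixed in the text; marked in Table 2 |
| Booking before 25 weeks | Secondary outcome; close to the payment condition | Table 2 only |
| Maternal smoking | Additional outcome; advice might change it | Fixed in the text; marked in Table 2, including during pregnancy |
| Gestational age at delivery | Secondary outcome | Table 2 only |
| Maternal nutrition | Named intention of the grant (Primary outcome) | Unmeasured (Table 2), so not adjusted for |

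The first four rows are in conflict with a total-effect target. The fifth is not: that route is not itself adjusted for.

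**2. The plan's benchmark.** The Sample size section gives power 0.90 for 7 g with intraclass correlation 0.05, and tests are two-sided. No birth-weight SD is given, so this cannot be reproduced directly. It implies SE = 7 / (1.960 + 1.282) = 2.16 g.

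- At 56 000 births a year, 25 grant months give 116 667 births and 63 + 32 = 95 other months give 443 333.
- With SE = SD × √[DEFF × (1/116 667 + 1/443 333)] and DEFF = 1 + (56 000/6505 − 1) × 0.05 = 1.38, the implied SD is 559 g.
- With no design effect it is 656 g. With all births per zone (DEFF 5.25) it is 286 g.

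The 7 g figure is attainable under some of these readings and is not shown to be wrong. It serves here only as a yardstick.

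**3. What adjusting for smoking could remove.** The Introduction gives 162–377 g per smoker. The fall in prevalence is my assumption.

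- 1 point: 0.01 × 162 = 1.6 g to 0.01 × 377 = 3.8 g.
- 2 points: 0.02 × 162 = 3.2 g to 0.02 × 377 = 7.5 g.
- For 7 g: 7/377 = 1.9 points to 7/162 = 4.3 points.

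**4. Consequence for power.** Suppose the total effect is 7 g and a share f passes through adjusted variables. Remaining effect = 7 × (1 − f), and power = Φ(remaining/2.16 − 1.96).

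| f (assumed) | Remaining effect | Power |
|---|---|---|
| 0 | 7.0 g | 0.90 |
| 10% | 6.3 g | 0.83 |
| 25% | 5.25 g | 0.68 |
| 50% | 3.5 g | 0.37 |
| 75% | 1.75 g | 0.13 |

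The SE is held fixed. Adjusting for a strong predictor such as gestational age would also lower it, so the net loss of power for that variable is smaller than shown. Nothing in the document selects a row.

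**5. Literal scope.** Read as written, adjusting all analyses for the listed covariates adjusts gestation at booking and maternal smoking for themselves. Table 2 leaves those cells empty. The two statements must be reconciled.

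**The case against.** The best argument for keeping booking and smoking is confounding. Exposure is defined by calendar dates. The Statistical analysis section reports that booking-appointment policy was under change from 2008, with all Health Boards to comply by March 2011, which overlaps most of the April 2009 to April 2011 window. The March 2006 smoking ban also shifted smoking. Leaving both variables out could credit the grant with another policy's effect. This stands, and it is why a booking- and smoking-adjusted model should still be reported. It does not justify that model as the only estimate, since adjustment removes the grant's own effect through these variables along with the rival policy's. The ban is also addressed by the planned analysis starting in April 2006.

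Timing matters too. Booking, and smoking recorded at booking, normally precede the 25-week payment. They can carry the incentive or advice route but not the cash route. This also stands.

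Univariable models are planned, but a grant-only model would omit trend and season and so would not be the interrupted time-series estimate. The simplest model is said to adjust for relevant factors, without naming a set that leaves the mediators out.

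A reader might infer that the adjusted models discard most of the effect. The document gives no mediated share, and the nutrition route is unmeasured and not itself adjusted for. A reader might also take gestational age as fixed in the model and as a pathway the grant was designed to use. It appears only in Table 2, as a covariate to be considered, and the protocol describes it only as a secondary outcome.

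**Conclusion.** The point holds in limited form. The text fixes adjustment of the birth-weight models for gestation at booking and smoking, and Table 2 puts forward gestational age at delivery, booking before 25 weeks and in-pregnancy smoking, although the protocol treats all of these as outcomes. The adjusted coefficient is therefore not cleanly the total effect, and no target effect is stated.

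The size of the omission is unknown. The 1.6 to 7.5 g illustration rests on an assumed 1 to 2 point fall in smoking. It shows that the omission could matter against a 7 g benchmark, which the protocol itself says is not a clinical threshold. It does not show that a working grant would be reported as null. Nor does the Economic analysis section say which coefficient enters the cost-effectiveness model.

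The self-adjustment of the booking and smoking outcomes is most likely loose wording, but it contradicts Table 2.

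**What to change.** - State that the target is the total effect of the grant on birth weight, and that this estimate feeds the economic model.
- Make the primary birth-weight model one adjusted for trend, season and covariates the grant cannot change, such as maternal age, parity, height, marital status, social class, the deprivation index's income domain, urban or rural residence, child's sex, pre-existing diabetes and smoking before pregnancy. Leave out gestational age at delivery, both booking variables and smoking in this pregnancy.
- For the other Table 2 covariates (for example weight at booking, hypertension, infection, alcohol, drug misuse), say for each whether the grant could alter it, and place it accordingly.
- Report beside the primary model a labelled secondary model that adds booking and smoking, with the concurrent booking policy and smoking ban as the reason, and a further mechanism model that adds gestational age.
- Replace the blanket adjustment sentence with Table 2's outcome-specific lists, so that no outcome is adjusted for itself.

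The cost is rewording and one or two model runs. Precision falls without gestational age: if it explains a share r of the residual variance, the SE rises by 1/√(1 − r), which is 1.05 for an assumed r of 10%, 1.20 for 30% and 1.41 for 50%. The primary estimate may also include part of the concurrent booking-policy effect. Reporting the models together makes that visible.
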